### Intervention

At the start of a care program at the Rotterdam youth care organisation every youth care professional sets, together with the youngster, certain goals to be reached during the care program. These goals can relate to the individual, school, work, family and positive leisure time activities. In the experimental region, specific attention is paid to sport participation as a positive leisure time activity. To increase the attention for sport as a positive leisure time activity, a Care Sport Connector (CSC) is appointed to act as a boundary spanner to connect youth care and sport. As a key-player in the network, the CSC is able to spark initiatives of collaboration between youth care professionals and organised sport clubs, and to identify local sport organisations that are capable of building conducive sport environments. The CSC will bring existing collaborations with local sport clubs to the attention of youth care professionals and will facilitate initiatives of the youth care professionals to make use of sport interventions.

It is expected that a training among the youth care professionals and collaboration with a Care Sport Connector (CSC) in the experimental group will translate to more sport participation among the youngsters of these professionals. The CSC will motivate and train the youth care professionals in the experimental condition to integrate sport activities in the care that they deliver. At the start of every care program, the youth care professional in the experimental regions are expected to inventory, together with the youngsters, the possibilities of sport participation during the care program. The youth care professionals are also expected to be involved in guiding the youngsters to local sport organisations.

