Training of the youth care professionals by the CSC will exist of various activities, such as interactive workshops, individual face-to-face sessions, and provision of written (online) information. Various topics will be discussed during these events that are relevant for the youth care professionals, for example focusing on practical barriers that they may encounter when guiding their youngsters to local sport organisations (such as money constraints, ethical issues and lack of parental support). These topics were selected after conducting several interviews with youth care professionals discussing their view of the inclusion of sport in youth care practices. During the intervention, additional events may be organised that match the needs of the youth care professionals and the CSC. As such, the training of the youth care professionals can be seen as coaching-on-the-job and the activities can be adapted to individual needs. All activities that take place will be carefully monitored and recorded, so that in the end a precise description of the actual intervention can be given. The activities of the CSC will continue after the end of this study and will be expanded to other regions of the Rotterdam youth care organisation as well.

Within the experimental regions, specific attention is also paid to the socio-pedagogical climate at the local sport clubs. A pedagogue is employed in the experimental regions to support the local sports clubs in their efforts to create a positive learning environment for all children. Several elements of the socio-pedagogical climate receive specific attention such as the setting and maintenance of basic rules at the sport clubs, improving the pedagogical qualities of the trainers and increasing the involvement of parents at the sport club. Similarly to the activities conducted by the CSC, the activities of the pedagogue are documented during the intervention to be able to provide a clear description at the end of the project.

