#### Study design and procedure

To test these hypotheses, quantitative data will be collected at three time points during the intervention. Data will be collected at baseline (i.e. when the youngsters enter the care program), after six months follow-up (i.e. at the end of the care program and intervention) and after 18 months follow-up (see Figure 2). The data of the baseline measurement and of the first follow-up will be collected using paper and digital questionnaires administered by the youth care professional. During the second follow-up, a digital and a paper questionnaire will be send to the youngsters who have left the youth care organisation at that point. If necessary, the researchers will go door-to-door to increase the response rate.

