#### Data analysis

Quantitative data will be analysed with the use of SPSS software (PASW statistics). The data will be analysed using multilevel modelling techniques. Single-level multiple regression models ignore the complexity of the hierarchical data within this current study and are likely to produce underestimated variances and standard errors. Multilevel modelling is especially suitable for repeated measurements of individuals nested in groups, as it is capable of examining correlated data and unequal variances [55]. In addition, because we have an unbalanced design, multilevel modelling will produce efficient estimates of the model parameters and covariance components. Within our study, the repeated measures (level 1 unit) of the individuals (level 2 unit) are nested in a region of the youth care organisation (level 3 unit). Hence, the observations are not independent from one another, because the individuals within one region are likely to be more similar as compared to other regions (i.e. between regions). For ordinal outcomes, generalized linear mixed models will be used to accommodate the different probability distributions of the data, as compared to continuous outcomes.

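### The multilevel model leaves out the youth care professional; standard errors for the sport term will be too small to the extent that sport participation and outcomes both cluster by professional

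*Protocol article*

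**What the plan says.** The Data analysis section under study aim 1 of the protocol article names the levels: "the repeated measures (level 1 unit) of the individuals (level 2 unit) are nested in a region of the youth care organisation (level 3 unit". Region is included because "the individuals within one region are likely to be more similar as compared to other regions". The same section gives the reason for not using a simpler model: "Single-level multiple regression models ignore the complexity of the hierarchical data within this current study and are likely to produce underestimated variances and standard errors". No section adds a level for the professional.

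Other sections describe what the professional does:

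- **Exposure.** The Intervention section directs the Care Sport Connector (CSC) at professionals: "The CSC will motivate and train the youth care professionals in the experimental condition to integrate sport activities in the care that they deliver". Training and collaboration with the CSC are expected to have an effect that "will translate to more sport participation among the youngsters of these professionals". Professionals also set care goals with each youngster, review the options for sport and are expected to help guide youngsters to clubs.
- **Variation between professionals.** The training is described as coaching on the job, in which "the activities can be adapted to individual needs".
- **Measurement.** Under Study design and procedure, the baseline (T0) and six-month (T1) data "will be collected using paper and digital questionnaires administered by the youth care professional". The 18-month (T2) questionnaire is sent to youngsters who have left care.

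Strengths and limitations adds that the intervention acts at CSC level and must pass through the professionals before it reaches the youngsters.

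**The concern.** The article argues that ignoring a layer of the hierarchy makes standard errors too small, and then leaves out a layer that its own description makes important. Two youngsters with the same professional share that person's attention to sport and, at T0 and T1, the person who administers the questionnaire. A random effect for five regions captures differences between regions. It cannot capture extra similarity among youngsters who share a professional within a region.

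Hypotheses 1 to 3 are about sport participation itself, which varies between youngsters and plausibly between professionals within a region. Hypothesis 4 takes the sport path into the mediation. If the standard error of the sport term is too small, intervals are too narrow and false-positive claims about sport are more frequent than 5%. The levels are stated, so this is a matter of what the model contains and not of detail left to a fuller plan.

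**Working it through.** **1. The article's own figures.** The Sample size section gives 244 participants for f = 0.20, three measurements, alpha 5% and power 0.80, and 436 at baseline after dropout.

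- A multivariate repeated-measures F test with noncentrality N × f² and degrees of freedom 2 and N − 3 reproduces 244. At N = 244 the noncentrality is 244 × 0.04 = 9.76 and power is 0.800; at N = 243 power is 0.798.
- Dropout: 244 / (0.80 × 0.70) = 435.7, so 436.

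Both figures are reproduced with no clustering term. They say nothing on how much outcomes or sport participation cluster by professional.

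**2. Inputs for the omitted level.** The article states the three model levels and five regions (three intervention, two control). It does not state the number of professionals, the caseload or any ICC. These are assumed:

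- m, youngsters per professional: 10 or 15
- ρy, outcome ICC within professional: 0.05 or 0.10
- ρx, sport participation ICC within professional: 0, 0.1 or 0.3

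**3. Formula.** For a between-youngster predictor, with the professional left out of the model:

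- true SE / reported SE = √(1 + (m − 1) × ρy × ρx)
- actual error of a nominal 5% test = 2 × (1 − Φ(1.96 / ratio))

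**4. Results.**

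| m | ρy | ρx | 1 + (m − 1)ρyρx | SE ratio | Actual error |
|---|---|---|---|---|---|
| 10 or 15 | 0.05 or 0.10 | 0 | 1.000 | 1.000 | 5.0% |
| 10 | 0.05 | 0.1 | 1.045 | 1.022 | 5.5% |
| 10 | 0.05 | 0.3 | 1.135 | 1.065 | 6.6% |
| 15 | 0.10 | 0.1 | 1.140 | 1.068 | 6.6% |
| 15 | 0.10 | 0.3 | 1.420 | 1.192 | 10.0% |

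**5. Checks on the formula.** A variance calculation used five regions, about 400 to 450 youngsters and person-mean outcomes. The true model had a professional effect; the fitted model had only region and youngster.

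- With m = 10, ρy = 0.05 and ρx = 0.3, reported SE / true SE was 0.926 and actual error 7.0%.
- With ρx = 0, the ratio was 1.00 for every caseload and outcome ICC tried.
- For the region-level contrast between arms, the ratio stayed at 0.99 to 1.00, because the region effect absorbs the omitted variance.

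A separate simulation of within-region regression gave 5.3% error at m = 10, ρy = 0.05, ρx = 0.1; 6.2% with ρx = 0.3; and 9.6% at m = 15, ρy = 0.10, ρx = 0.3. All three sources agree on direction and approximate size.

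**6. Where the formula does not apply.** Sport participation is measured at T0, T1 and T2, so its coefficient can draw partly on change within a youngster. A professional intercept that is constant over time cancels from such within-person contrasts and causes no error there. A professional effect on change would not cancel.

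**The case against.** The strongest case on the other side is that nothing in the documents shows the effect to be material. Inflation requires both the outcome and the predictor to cluster by professional, and no ICC or caseload is given. Sport participation is each youngster's own report of a voluntary activity, so its ICC may be low. At ρx = 0.1, m = 10 and ρy = 0.05 the true standard error is only 2.2% larger. The trained-professional mechanism operates only in the experimental regions, and professionals do not administer T2. The article also does not say outright that each youngster has a single professional. All of this stands. It limits the size and makes the point conditional, but does not remove the mismatch between the stated model and the stated route of the intervention.

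A reader might infer more than the documents support:

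- **That standard errors are certainly too small, perhaps by half.** With m = 15, ρy = 0.10 and a sport ICC of 1.0, the formula gives a ratio of 1.549 and about 21% error. An ICC of 1.0 means that all youngsters of one professional have identical sport participation, which is implausible for an individual, voluntary activity.
- **That hypotheses 5 and 6 are equally affected.** The article does not say that sense of coherence clusters by professional. Motivational climate is perceived in the sport setting, and the pedagogue works on climate at the clubs, which points to clubs rather than caseloads.
- **That the arm comparison loses its protection because a region variance may be estimated as zero.** That is a separate problem of having only five regions. Omitting the professional does not create it.

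**Conclusion.** The point holds in conditional form. The stated model omits a level that the article makes the channel for sport exposure and the administrator of two of the three questionnaires. To the extent that sport participation and outcomes both cluster by professional, the sport term in hypotheses 1 to 3, and the sport path in hypothesis 4, will have standard errors that are too small. Over the assumed ranges in the table, true standard errors are about 2% to 19% larger than reported and actual error is about 5.5% to 10%. The caseload and both ICCs are assumptions, so the effect could be negligible. Because the size is unknown, it should be estimated from the trial's data, which requires that the professional is recorded.

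**What to change.** - Record an identifier for the youth care professional on the T0 form, which that professional already administers.
- In the models with the sport term, add a random intercept for the professional between youngster and region, using the professional recorded at T0. Keep region in the model.
- State in advance that professional-clustered standard errors will be used if this model does not converge.
- Report the professional-level ICC.

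The cost is one extra field, one extra variance component and somewhat wider intervals for the sport term. If the ICC is near zero, the results will hardly change. The identifier should be in place before baseline collection, since it may not be recoverable later.

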### Study aim 2: Life experiences of socially vulnerable youth in sport context

#### Study design and participants

Interviews will be conducted with youngsters in the experimental regions during their time at the Rotterdam youth care organisation. The youth care professionals will be asked to identify youngsters for whom sport participation seems to work out well (rich response sampling) [56]. Data is collected until data saturation is reached. In-depth interviews will be conducted that aim to understand the life experiences of the youngsters in the sport context that may contribute to enhanced life prospects. The interviews will be very open and aim to invoke narratives of the youngsters about their sporting activities. Investigating the experiences of the youngsters may enhance our understanding of how the social interaction (with sport coaches and peers) in the sport context may lead to improved life prospects. Czarniawska points out that narratives are *“…often substituting chronology for causality”* (p. 651) [57]. The data gathered via these in-depth interviews cannot provide evidence on the causal relation between sport and life prospects in a statistical sense. However, the data can provide insights on the meanings that youngsters attach to activities in the sport context and the perceived role these activities play in their personal development. The interviews will be audio-taped and transcribed intelligent verbatim style.

#### Data analysis

The transcripts of the interviews will be coded and analysed using software for qualitative data analysis (Atlas.ti). The data will be analysed following the hermeneutical approach which will allow us to review the experiences of the participants in their own words [58]. The hermeneutical approach emphasises interpretation of phenomena as articulated by the interviewees and, more importantly, interpreted by the researcher. Reaching understanding of these phenomena occurs in a cyclical process in which the researcher moves from the whole text to parts of the text, and vice versa. Parts of the text cannot be understood without looking at the whole text, and the whole text only makes sense when looking at specific parts of the text.

The experiences of the youngsters will be explored in the light of positive youth development theory and Antonovsky’s sense of coherence. Through reading the transcripts and interpreting the described phenomena, the experiences of the youngsters can be contextualised and understood in light of these theories. The hermeneutical approach consists of a dialogue between the researcher and the text and, hence, the understanding of phenomena is always biased [59,60]. The aim of the hermeneutical study is then to provide one unique and partial understanding of how youngsters experience sport activities in relation to their personal development.

### Study aim 3: social conditions

To study the role of social conditions in the effect of sport participation on life prospects, two different research approaches are adopted. The first approach quantitatively assesses the moderating role of a motivational sport climate in the relationship between sport participation and life prospects. The second approach qualitatively examines the role of the sport coaches in creating social conditions that could improve the personal development of socially vulnerable youth.

### Quantitative sub-study: the moderating role of motivational sport climate

To study the influence of a motivational sport climate on the relation between sport participation and life prospects, a scale measuring sport climate will be included in the questionnaires administered to assess the causal effect of sport participation (i.e. study aim 1). The Motivational Climate Scale for Youth Sports (MCSY) contains two subscales for a mastery-motivational and an ego-motivational climate and assesses the youth’s perceived motivational sport climate. This scale will be included in the second and third questionnaire administered at, respectively, 6 months and 18 months of follow-up [44]. The following hypothesis (hypothesis 6) was formulated: The positive effect of sport participation on life prospects is moderated by motivational sport climate. The moderating effect of motivational sport climate will be statistically analysed using multivariate regression techniques (multi-level modelling).

### Qualitative sub-study: the role of sport coaches in creating positive social conditions

#### Study design and participants

Interviews will be conducted with sport coaches about their coaching practices to see how they create situations in which positive life experiences can arise for socially vulnerable youth. A list of sport coaches will be created after consultation with the youth care professionals who are asked to keep track of the sport clubs their youngsters are joining. Sport coaches will be selected from this list in such a way that they represent a wide variety of sport types. All the interviews will be conducted within the Rotterdam context with sport coaches that give training to the youngsters of the youth care organisation. The interviews will be semi-structured and conducted with the purpose to reveal how sport coaches engage in interaction with the youngsters of the youth care organisation. The coaches will be invited to share their experiences of training these youngsters. In addition, specific questions are asked that address the three SOC-components. This will allow us to review the role of the sport coach in creating life experiences that could lead to enhancements in SOC. The interviews will be audio-taped and transcribed intelligent verbatim style.

#### Data analysis

Transcripts of the interviews will be used for qualitative analysis in Atlas.ti. A thematic analysis will be conducted on the data following the guidelines of Braun and Clarke [61]. They propose six phases for a thematic analysis starting with familiarising yourself with the data and generating initial codes. The codes are then ordered in themes and rearranged to generate a thematic map of the data. In the final phase of the ongoing analysis, the themes are reviewed in relation to the whole text and the literature. The analysis will be deductive in nature, based on the sense of coherence theory. Themes will be established *a priori*, based on the current literature about the SOC theory, and mapped on the data. In addition, codes not fitting with one of the pre-designed themes will be examined to see if they can form a new theme.

### Study aim 4: elements of successful partnerships

#### Study design and participants

To identify elements of successful partnerships between youth care organisations and local sport clubs, qualitative data will be collected throughout the study by conducting in-depth interviews with youth care professionals, the Care Sport Connector (CSC) and stakeholders in the local sport clubs. At least five interviews with randomly selected youth care professionals and five interviews with randomly selected stakeholder in the organised sport clubs will be conducted in both the intervention and the control area. Three interviews with the CSC will be employed in the intervention area. Additional interviews will be conducted if data saturation is not reached after this number of interviews. The interviews will be audio-taped and transcribed (intelligent verbatim style).

In the interviews with the youth care professionals, the stakeholders in the local sport clubs and the CSC, the HALL-framework will be used as a starting point. Consequently, the participants will be asked about personal and organisational factors that might influence the quality and performance of the partnership, and factors related to the organisation of the partnership that may help to deal with personal and organisational differences. In addition, the researchers ask participants about the goals of the partnership, to what extent they think they have reached these goals and what factors helped to reach these goals. As a result, it is possible to investigate associations between the occurrence of specific factors (personal factors, institutional factors, and factors on the level of the organisation of the partnership) and how the participants involved in the partnership perceive the results of the partnership.

#### Data analysis

The data analysis will take place in three stages [62]. At first, the researchers will read all the data and will develop a codebook in which the HALL-framework functions as a starting point. Hence, a deductive coding approach is used in which the codes in the codebook refer to the three different factors of the HALL framework: the personal factors, the institutional factors and the factors related to the organisation of the partnership. A fourth element of the codebook will be the perceived performance of the partnership. Reading all the data before coding makes it possible to create codes for specific results of the partnership, as well as to expand the codebook with personal factors, institutional factors and factors relating to the organisation of the partnership that are not yet part of the HALL-framework.

In the second stage, the data will be analysed and presented in tables and summaries. These tables and summaries will represent the frequency participants mention specific factors in the partnership between the youth care organisation and the local sports clubs, and what the participants perceive as the performance of the partnership. To investigate which personal factors, institutional factors and factors relating the organisation of the partnership determine the performance of the partnership, associations between the occurrence of the different factors and the performance of the partnership will be explored in Atlas.ti. The presented findings will serve as a starting point for the third phase: validation of the data. Validating the data will occur by four of the nine validity procedures presented by Creswell [62]. First of all, to avoid researcher bias, two researchers will be involved in the process of data coding and data analysis. Secondly, after analysing and representing the findings, all the data will be read to search information that disconfirms the evidence. Thirdly, the researchers will confront the participants with their interpretations via e-mail or via a focus group meeting. Through this so-called member checking, participants can confirm if the researchers accurately represented their reality. Fourthly, all research activities and decisions made throughout the research process will be documented. A researcher who is not closely involved in the research project will be asked to monitor and review this documentation.

